### Hypotheses/Research Question

Our first hypothesis is that a narrative-informed, group-based early intervention for postpartum women who have had a traumatic birth experience will be feasible and acceptable. Our second hypothesis is that the intervention will decrease symptoms of postpartum depression, postpartum anxiety, and/or postpartum post-traumatic stress disorder (PTSD) in women with traumatic birth experiences.

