### Allocation and Concealment

This pilot trial included an IG (who received the intervention immediately after recruitment) and a WCG (who were allocated to a waitlist during the same observation period as the intervention. Although there were no restrictions on outside care for the WCG, no intervention or support was actively offered to these participants. HM monitored the mental health of participants in the WCG (across the outcome measures administered at various timepoints; see Table 1) and alerted the team to any observed deterioration. A recent pilot feasibility trial conducted in Australia noted that people typically wait 6 months or longer to access mental health services [43]. Once the study with the IG concluded, the WCG received the full intervention, which involved a wait time of 6 weeks, significantly less than the typical waitlist.

A randomization sequence in alternating block sizes of 4 and 6 was generated from an online sequence generator by author PJT. The randomization sequence was revealed to the research assistant (HM) and only after completion of the baseline and eligibility measures. At that time, the research assistant informed participants of the intervention start date based on their allocation to either the IG or the WCG.

**Table 1 table1:** Data collection timeline.

Measure	IG^a^ timepoints					WCG^b^ timepoints			
	T1^c^	T2^d^	T3^e^	T4^f^	T1		T2	T3	T4
City BiTS^g^	X^h^	X	X	—^i^	X		X	X	X
EPDS^j^	X	X	X	—	X		X	X	X
PASS^k^	X	X	X	—	X		X	X	X
GCS^l^	—	—	X	—	—		—	—	X
CSQ-8^m^	—	—	X	—	—		—	—	X

^a^IG: intervention group.

^b^WCG: waitlist control group.

^c^T1: prior to session 1 for the IG.

^d^T2: after session 3 for the IG.

^e^T3: after session 6 for the IG.

^f^T4: after session 6 for the WCG.

^g^City BiTS: City Birth Trauma Scale.

^h^X: applicable.

^i^Not applicable.

^j^EPDS: Edinburgh Postnatal Depression Scale.

^k^PASS: Perinatal Anxiety Screening Scale.

^l^GCS: Group Cohesiveness Scale.

^m^CSQ-8: Client Satisfaction Questionnaire.

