#### Outcomes

The following measures were administered according to the schedule depicted earlier in Table 1.

Treatment acceptability was assessed using the Group Cohesiveness Scale (GCS) [46] and the Client Satisfaction Questionnaire (CSQ-8) [47].

The GCS is a 7-item self-report measure assessing the level of cohesiveness in group therapy settings. The scale has strong psychometric properties and is a brief measure of group cohesiveness that can be used in psychiatric settings [46]. The CSQ-8 is a widely used 8-item scale measuring client satisfaction with mental health services. It is a subscale of the original Client Satisfaction Questionnaire-18, which has robust psychometric properties and, combined with its brevity, is a useful brief measure of client satisfaction [48]. The CSQ-8 has been used successfully in the provision of psychological interventions via telehealth (ie, videoconferencing) for conditions such as depression [49].

Treatment feasibility was assessed using indicators of treatment adherence and retention. Based on Wright et al’s [24] research on a virtual psychotherapy group for postpartum mothers, a rate of 70% was set to determine feasibility with respect to individual participant attendance across all the six sessions of the intervention, as well as overall retention (determined by the completion of all postintervention measures after session 6).

Postpartum depression was assessed using the EPDS [50], a 10-item self-report questionnaire widely used to screen for postpartum depression. It assesses symptoms experienced in the past 7 days, with higher scores indicative of a greater endorsement of depressive symptoms. The EPDS has demonstrated good reliability and validity in postpartum women [51] and has been validated for routine postnatal screening in Australia [52].

Postpartum anxiety was assessed using the Perinatal Anxiety Screening Scale (PASS) [53], a 31-item self-report questionnaire designed to screen for anxiety in both antenatal and postpartum women. Developed and validated for use in Australia [53], PASS provides cutoffs for differentiating between minimal, mid-moderate, and severe anxiety [54]. Its strong psychometric properties have led to its cross-cultural use and translation to other languages.

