### Data Analysis

#### Quantitative Data

All analyses will be based on the intention-to-treat principle. The quantitative data analyses will involve repeated-measures ANOVA entering the main effects for group, time, and group×time interaction, assuming α<.05 to denote a significant effect between the IG and the WCG for continuous study outcomes (City BiTS, EPDS, PASS). Assumption testing will examine normality using the Shapiro-Wilk test and sphericity using the Mauchley test of sphericity. Transformation and Huynh-Feldt correction will be applied, respectively, in the case of violation of these assumptions. The therapy process measures will be analyzed for between-group differences to determine the acceptability of the group intervention. As a feasibility and acceptability study, testing the proof of principle, our analyses will provide an estimate of mean (SD) change data and effect sizes to inform a larger trial in the future. The assessment of acceptability and feasibility postdelivery of the intervention, in both the IG and after the last session of the WCG, will afford the trial more quantitative data to identify aspects of the intervention that were perceived as beneficial and preferred.

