**Figure 1 figure1:**
[figure not shown]
Flowchart of the pilot trial procedure. IG: intervention group; WCG: waitlist control group.

To determine treatment acceptability, GCS-7 and CSQ-8 scores will be totaled for each participant, and a range of scores will be examined, including the central tendency score for each group. Higher scores will indicate greater treatment acceptability on both measures. Treatment feasibility will be determined by using attendance and retention metrics, with a threshold of 70% established as the criterion for feasibility drawn from recent research on virtual psychotherapy groups for postpartum mothers [24]. This threshold will apply to both individual participant attendance across all six sessions and overall retention, as measured by completion of postintervention measures across both groups. These predetermined benchmarks will provide clear criteria for determining whether the intervention warrants investigation in a larger trial.

The mental health outcome measures (EPDS, PASS, and City BiTS) will be scored according to the developer instructions. The last observation carried forward (LOCF) approach will be used to deal with any missing values, which involves replacing each missing value of a participant with the last observed value for that participant. The LOCF was chosen for its simplicity and frequent use in clinical trials [58]. As this is predominantly a feasibility and acceptability pilot study whose sample size is insufficiently powered to demonstrate statistically significant treatment effects, the LOCF was chosen over other more complex imputation methods that may not offer substantial benefits at this early stage. The average scores will be compared across the IG (who had these measures administered prior to, during, and after the intervention) and the WCG (who completed measures while they were on the waitlist, as well as after they received the intervention).

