### Study Limitations and Future Directions

This study has several limitations that warrant consideration. First, the statistical power for detecting significant changes in the mental health outcome measures is limited owing to the small sample size (n=9) in this pilot trial, and the use of single imputation methods (eg, LOCF) to deal with missing values is generally not recommended as it is based on the assumption that outcomes do not change if a participant does not fill in a specific measure [58]. However, the primary aim of this project is to examine the feasibility and acceptability of delivering such an intervention, not to comment on significant treatment effects. Further, as we are adopting an embedded mixed methods approach, it is anticipated that the qualitative data will provide a rich understanding of the processes facilitating change as a result of the intervention. If feasibility and acceptability are demonstrated in this study, then future research can look at using this intervention in large-scale trials with a priori power calculations to evaluate statistical significance. In this instance, multiple imputation methods would be recommended to deal with missing values in order to provide more robust estimates.

Second, it is possible that there has been a selection bias owing to recruitment through social media and health care professionals. Potential participants were to send in an EOI if they wished to participate in the study and could have had higher digital literacy, less perceived stigma, and greater help-seeking tendencies than other eligible persons who did not submit an EOI. Further, postpartum women outside of the geographical region under study, and those with infants older than 6 months of age, were not eligible to participate in this study, which meant that the intervention could not be offered even when they reached out (sent an EOI). Participants who were deemed ineligible were provided with alternate mental health support resource options that they could access. This recruitment strategy also potentially limited the cultural diversity in potential participants. Future research with larger trials could seek to deliberately recruit participants from culturally diverse backgrounds, which could speak to this intervention’s broader applicability.

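### Acceptability is to be determined from a between-arm difference on GCS and CSQ-8, taken after both arms have had the same therapy, and the descriptive alternative sets no acceptable level

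*Protocol article*

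**What the plan says.** The first hypothesis (Hypotheses/Research Question) is that the intervention for women "who have had a traumatic birth experience will be feasible and acceptable". The Outcomes section names two acceptability measures, the Group Cohesiveness Scale (GCS) and the Client Satisfaction Questionnaire (CSQ-8).

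Two places say how acceptability will be judged:

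- **Data Analysis, Quantitative Data:** "The therapy process measures will be analyzed for between-group differences to determine the acceptability of the group intervention".
- **The text following Figure 1:** GCS and CSQ-8 are totalled for each participant, and the range and each group's central tendency are examined. "Higher scores will indicate greater treatment acceptability on both measures".

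Table 1 (Allocation and Concealment) places GCS and CSQ-8 at one timepoint per arm: T3 for the intervention group (IG) and T4 for the waitlist control group (WCG). The footnotes define these as "T3: after session 6 for the IG" and "T4: after session 6 for the WCG". The same section says that the waitlist arm received the whole intervention once the first arm had finished.

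The only numerical criterion is 70%, applied to session attendance and to completion of the postintervention measures. The article then says: "These predetermined benchmarks will provide clear criteria for determining whether the intervention warrants investigation in a larger trial". Study Limitations and Future Directions makes large-scale trials conditional: "If feasibility and acceptability are demonstrated in this study". The Conclusion repeats that condition.

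**The concern.** A between-arm comparison tells us about a treatment only if the arms differ in the treatment they have had. For GCS and CSQ-8 they do not: every woman rates the same six-session programme after completing it. The stated determinant of acceptability therefore answers another question, namely whether women treated at once and women treated about six weeks later, in a different therapy group, scored differently.

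Acceptability is half of the first hypothesis and a condition for a larger trial. If the Quantitative Data sentence is followed, the reported result will not bear on it. If the text after Figure 1 is followed, the result bears on it, but nothing says which scores would count as acceptable.

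**Working it through.** The article gives no acceptability target, mean or SD, so there is no figure of its own to reproduce. The check is mainly a reading of Table 1 against the analysis text.

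**Step 1. Which measures are meant.** The article does not define therapy process measures. The same paragraph assigns City BiTS, EPDS and PASS to the repeated-measures ANOVA. That leaves GCS and CSQ-8, which Outcomes names as the acceptability measures.

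**Step 2. Exposure when measured (Table 1).**

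| Arm | GCS and CSQ-8 collected | Sessions received by then |
|---|---|---|
| IG | T3 only | six |
| WCG | T4 only | six |

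**Step 3. What the contrast estimates.** Let μ be the common level of acceptability and let δ(IG) and δ(WCG) be the effects of timing and therapy group in each arm. The expected difference is

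(μ + δ(IG)) − (μ + δ(WCG)) = δ(IG) − δ(WCG).

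The level μ cancels, so uniformly low and uniformly high scores give the same expected difference. The Qualitative Data section has analysts read the two initial sessions together, which implies one therapy group per arm. Timing and therapy group then cannot be separated.

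**Step 4. Is there a criterion elsewhere?**

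- Totals, range and central tendency: a direction is given, but no level.
- 70%: labelled a feasibility criterion and tied to attendance and retention.
- Abstract, Results: lists group cohesion with attendance and retention as metrics, without a level.
- Qualitative analysis: may show which elements were acceptable, but sets no criterion.

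**Step 5. Precision of the summary that would answer the question.** Inputs: 9 randomised, 4 to IG and 5 to WCG (Abstract, Results). All are assumed measured. The 95% half-width for a mean, in SD units, is t(0.975, n−1)/√n:

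- n = 9, pooled: 0.769
- n = 4, IG alone: 1.591
- n = 5, WCG alone: 1.242

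The pooled figure treats the women as independent. With groups of 4 and 5, the design effect is 1 + [(4² + 5²)/9 − 1] × ICC = 1 + 3.556 × ICC. The documents give no ICC, so a range is assumed:

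- ICC 0.1: design effect 1.36; half-width 0.769 × √1.36 ≈ 0.90 SD
- ICC 0.3: design effect 2.07; half-width 0.769 × √2.07 ≈ 1.11 SD

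Both are before any loss of degrees of freedom from having only two groups.

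For the proportion of women reaching a floor, exact 95% intervals, again assuming independence, are 40% to 97% for 7/9, 52% to 99.7% for 8/9 and 66% to 100% for 9/9.

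**The case against.** The strongest reply is that the between-arm sentence is not the whole plan. The text after Figure 1 says acceptability is to be judged from participants' totals and each group's central tendency. That route looks at the level of the scores, and two equally dissatisfied groups would be visible in it. This stands: the article has a workable route beside an unsuitable one, and the two conflict.

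A reader might go further in three ways that the documents do not support.

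- **That a non-significant difference would be read as proof of acceptability.** No test, significance level or decision rule is stated for these measures; the .05 level is tied to City BiTS, EPDS and PASS. If a two-sided t-test at .05 were assumed, 4 against 5 women would need an observed difference of 2.365 × √(1/4 + 1/5) = 1.59 SD, and power would be 25% at a true difference of 1 SD. These figures illustrate an assumed test. Sample Size and Study Limitations already disclose the lack of power.
- **That the acceptability hypothesis cannot fail.** Low totals could lead the authors to a negative judgement, and the qualitative work could too. The supportable statement is narrower: no score level is defined as acceptable.
- **That the article claims an acceptability benchmark it lacks.** The sentence on predetermined benchmarks directly follows the 70% threshold and can be read as covering feasibility only.

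A scale cut-off may also sit in a fuller document that is not shown, so its absence alone would be weak ground. The point rests on the contrast the article does state, its conflict with the descriptive route, and the condition placed on a larger trial.

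**Conclusion.** The concern holds in a limited form and should be fixed. The Quantitative Data sentence names a comparison that carries no information on the level of acceptability, because both arms have had the same six sessions when GCS and CSQ-8 are collected. The text after Figure 1 describes a different and more suitable analysis but sets no acceptable level, while progression depends on acceptability being shown.

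The conclusion about the contrast rests on Table 1 and on reading the process measures as GCS and CSQ-8; it needs no numerical assumption. The precision figures assume all nine women are measured. The 0.77 SD half-width also assumes independence, and the 0.90 to 1.11 SD range assumes an ICC of 0.1 to 0.3. At this size any acceptability criterion is a descriptive progression rule and not a powered test.

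**What to change.** 1. In Quantitative Data, remove the between-arm comparison as the determinant of acceptability and bring the sentence into line with the text after Figure 1.
2. Make the main acceptability summary the individual GCS and CSQ-8 totals and the pooled mean over all treated women (IG at T3 plus WCG at T4). Keep the arm split as description. Label any confidence interval descriptive, because the women were treated in two therapy groups.
3. If the scores have not been opened, first fix a floor for each scale, justified separately for each: GCS measures cohesion, so a satisfaction anchor does not evidently suit it. Add a sensitivity count in which non-responders are taken as not meeting the floor. Each scale is collected once, so there is no earlier value to carry forward. For example, seven responders all meeting the floor would be 7/7 among responders but 7/9 (78%) in the sensitivity count.
4. If the scores have been seen, report acceptability descriptively and do not call it demonstrated. The Abstract puts final data collection in December 2024 with analysis under way, so the authors should state which case applies.

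The cost is revised wording and one summary table, with no new data. The drawback is that acceptability may be found not met, or may only be described.

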#### Qualitative Data

Audio recordings of all group sessions were transcribed verbatim for qualitative analyses to identify the key themes salient in the treatment of traumatic birth experiences. The transcribed data from the six intervention sessions across both the IG and the WCG will be subjected to qualitative data analysis in order to better understand therapeutic processes that support change. Specifically, comprehensive process analysis (CPA) [57] will be adopted. CPA is an interpretive, qualitative research method used for analyzing therapy and is specifically designed to identify elements that could facilitate or hinder therapeutic progress [57]. The analysis will encompass three broad domains: context, key responses, and effects. Elliot et al [57] described four levels of *context* that must be explored: background (factors bringing participants into treatment, which in this study include experiences of birth trauma, previous coping styles, etc), presession context (referring to relevant events that could occur between sessions, eg, preparing a narrative of one’s birth story), session context (eg, therapeutic alliance and session tasks such as sharing one’s birth story, outsider witness), and, finally, episode context (conversational episodes pertaining to a significant event in therapy). An analysis of *key responses* relates to therapist or client responses perceived to be most helpful [57]. This analysis can include actions by the clinician or client, the style adopted, the nature of the content, and the quality of delivery. Finally, *effects* will be documented, aiming to track immediate and delayed consequences of the events within a session or across treatment.

Two coauthors will serve as CPA analysts (CS and HF), the former of whom is also the intervention facilitator. Both CS and HF are experienced in qualitative data analysis. Each analyst will independently review session transcripts (looking at the two initial sessions together, the two second sessions together, and so on) to identify significant process events and extract meanings with respect to context, key responses, and effects. The analysts will also maintain a reflective journal through this process. Once this step is complete, the analysists will meet in the presence of another coauthor (SC), also experienced in qualitative data analysis and not part of the intervention, who will assist in developing consensus through open dialogue, while ensuring that all perspectives are considered and discussed adequately. The multiauthor discussion and review, alongside considerations in the reflective journal, will support the trustworthiness and rigor of the analysis and ensure the analysis best reflects the data and process elements. With this process, we aim to produce a comprehensive understanding of which narrative intervention elements that effectively support birth trauma recovery in a telehealth group setting and which require modification, directly informing intervention refinement for the future. The embedded mixed methods design will allow details of the processes of change in the intervention to complement qualitative findings around feasibility and effectiveness. Outcome data will also be used to triangulate qualitative findings to further support which elements of change were and were not acceptable or useful for participants.

**Figure 1 figure1:**
[figure not shown]
Flowchart of the pilot trial procedure. IG: intervention group; WCG: waitlist control group.

To determine treatment acceptability, GCS-7 and CSQ-8 scores will be totaled for each participant, and a range of scores will be examined, including the central tendency score for each group. Higher scores will indicate greater treatment acceptability on both measures. Treatment feasibility will be determined by using attendance and retention metrics, with a threshold of 70% established as the criterion for feasibility drawn from recent research on virtual psychotherapy groups for postpartum mothers [24]. This threshold will apply to both individual participant attendance across all six sessions and overall retention, as measured by completion of postintervention measures across both groups. These predetermined benchmarks will provide clear criteria for determining whether the intervention warrants investigation in a larger trial.

The mental health outcome measures (EPDS, PASS, and City BiTS) will be scored according to the developer instructions. The last observation carried forward (LOCF) approach will be used to deal with any missing values, which involves replacing each missing value of a participant with the last observed value for that participant. The LOCF was chosen for its simplicity and frequent use in clinical trials [58]. As this is predominantly a feasibility and acceptability pilot study whose sample size is insufficiently powered to demonstrate statistically significant treatment effects, the LOCF was chosen over other more complex imputation methods that may not offer substantial benefits at this early stage. The average scores will be compared across the IG (who had these measures administered prior to, during, and after the intervention) and the WCG (who completed measures while they were on the waitlist, as well as after they received the intervention).

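### LOCF is the only rule for missing symptom scores: if any are missing, it can bias the arm difference either way and distort, usually understate, the SD of change meant for the larger trial

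*Protocol article*

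**What the plan says.** The text after the Figure 1 caption in the Protocol article sets the rule for the three symptom scales: "The last observation carried forward (LOCF) approach will be used to deal with any missing values". It defines this as "replacing each missing value of a participant with the last observed value for that participant". The reason given is that "The LOCF was chosen for its simplicity and frequent use in clinical trials", together with the argument that an underpowered pilot gains little from more complex imputation. The article describes no other method and no sensitivity analysis.

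Three other places bear on the rule:

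- Study Limitations and Future Directions says that single imputation such as LOCF "is generally not recommended as it is based on the assumption that outcomes do not change" when a measure is not completed. It recommends multiple imputation for the larger trial.
- Hypotheses/Research Question predicts that depression, anxiety and/or PTSD symptoms will fall with the intervention.
- Data Analysis, Quantitative Data plans a group×time test at .05 and states that "our analyses will provide an estimate of mean (SD) change data and effect sizes to inform a larger trial in the future". It also says that "All analyses will be based on the intention-to-treat principle".

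Table 1 schedules the symptom scales at T1, T2 and T3 in both arms, and again at T4 in the waitlist arm after that arm has received therapy.

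**The concern.** The rule imputes no change in a trial whose second hypothesis is change. The reasons given do not meet the difficulty. Low power is a matter of precision, whereas LOCF introduces bias. LOCF is also weighed only against more complex imputation, although a repeated-measures model fitted to the observed scores needs no imputation, and neither does a summary of observed change.

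Mean change, its SD and the effect size are named as inputs to the next trial. If they are distorted here, multiple imputation in that later trial comes too late to protect its sample size.

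The waitlist T4 visit is a separate problem. A missing T4 score would be filled with the T3 score, so a value measured before therapy would count as an outcome after therapy.

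**Working it through.** There is no power or sample-size figure to reproduce: the target of 16 rests on budget, timelines and group size. The documents give no SD, effect size, natural course or missing rate. All means, SDs and correlations below are assumptions.

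**Inputs from the article.** Nine women were randomised, 4 to the intervention group (IG) and 5 to the waitlist control group (WCG). Retention must reach 70%. With nine women, two losses leave 7/9 = 78%, which passes; three leave 6/9 = 67%, which fails. The largest loss compatible with the benchmark is therefore 2/9 = 22%. The benchmark counts measures completed after session 6, which for the waitlist arm is T4, so using 2/9 as the T3 rate is itself an assumption.

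**1. Weight of one missing score.** If baseline is carried, the woman's change becomes zero and her arm's mean moves by 1/4 = 25% (IG) or 1/5 = 20% (WCG) of her unobserved change.

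**2. Arm difference.** With baseline carried, missingness unrelated to outcome, mean changes μI and μW, and missing fractions pI and pW:

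expected LOCF difference = (1 − pI)μI − (1 − pW)μW, against a true μI − μW.

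| Assumed μI, μW | Missing | True | LOCF |
|---|---|---|---|
| -5, -2 | 1 of 4 IG | -3 | 0.75(-5) + 2 = -1.75 |
| -5, -2 | 1 of 5 WCG | -3 | -5 + 0.8(2) = -3.40 |
| -5, -2 | one in each arm | -3 | -3.75 + 1.60 = -2.15 |
| -5, -5 | 1 of 4 IG | 0 | -3.75 + 5 = +1.25 |
| -5, -5 | 1 of 5 WCG | 0 | -5 + 4 = -1.00 |

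The error goes both ways and can create a difference where there is none. If T2 is carried instead and half the change has occurred by then (assumed), the errors halve. The first row becomes (3(-5) − 2.5)/4 + 2 = -2.375, and the second becomes -5 + (4(2) + 1)/5 = -3.20.

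**3. SD of change, baseline carried.** With true SD s, mean change m and missing fraction p:

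Var(LOCF) = (1 − p)s² + p(1 − p)m².

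Take p = 2/9 and an assumed s = 6:

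- m = 0: (7/9)(36) = 28.0, SD 5.29, variance ratio 28.0/36 = 0.78.
- m = -4: 28.0 + (2/9)(7/9)(16) = 30.8, SD 5.55, variance ratio 30.8/36 = 0.85.

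For a fixed target difference, sample size is proportional to the variance, so a later trial would be understated by about 15-22%.

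**4. Limits of the SD result.** From the formula, the SD shrinks only if |m|/s < 1/√(1 − p). At p = 2/9 that is 3/√7 = 1.13; for 10%, 20% and 30% missing it is 1.05, 1.12 and 1.20. When T2 is carried to T3, the answer depends on the correlation structure. Simulation with score SD 5, 30% missing and mean changes of 0, -3, -5 and -8 gave:

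- AR(1) correlation 0.7: true SD 5.05; LOCF 4.73, 4.78, 4.87, 5.08.
- Compound symmetry 0.6: true SD 4.47; LOCF 4.47, 4.52, 4.62, 4.84.

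The SD is usually understated, but it can be unchanged or inflated.

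**The case against.** The authors disclose the weakness themselves and give reasons. The criteria for going on to a larger trial are attendance and retention, and the limitations section says the aim is not to comment on significant treatment effects. The acceptability scales are given once per woman, so there is nothing to carry forward. All of this stands and confines the point to secondary aims. It does not remove the bias from estimates that the article says will inform the next trial.

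No missing rate is reported. The abstract says IG data collection was finalised at all three timepoints, and vouchers were used to promote retention. Neither shows that the data are complete, but if nothing is missing, LOCF changes nothing.

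The practical weight is modest. With 7 degrees of freedom, a 95% interval for a pooled SD runs from about 0.66 to 2.04 times its estimate, which is wide beside a distortion of 8-12%. That limits urgency but does not justify adding an avoidable bias that usually runs in one direction.

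The alternatives also carry assumptions. A likelihood-based model relies on data missing at random, which cannot be tested here. Summaries of observed pairs leave out some randomised women, which sits less easily with intention to treat. Both need to be stated.

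A reader might infer that LOCF always shrinks the SD, or that 30% missing is the loss to plan for. The first fails for large mean changes and for some T2 carry-forward patterns. The second cannot occur in nine women who meet the benchmark.

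**Conclusion.** The point holds in conditional form. LOCF is prescribed against the article's own caveat and its own hypothesis, and the reasons given do not justify it. If scores are missing, the arm difference can move either way, by 25% or 20% of one woman's unobserved change for each woman lost after T1, and by less if T2 is carried. With baseline carried, 2 of 9 missing, an assumed SD of 6 and mean change of 0 to -4, the SD of change falls to about 5.3-5.5 and a later sample size is understated by about 15-22%. Change on the waitlist is an assumption; the documents give no natural course.

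It would go too far to infer that the trial's estimates are already biased or that its feasibility conclusion is at risk. No count of missing scores is given, and the feasibility criteria do not use imputed symptom scores.

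**What to change.** Drop LOCF as the main method.

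- Analyse all observed T1-T3 scores with a simple likelihood-based repeated-measures model with a random intercept. If it does not converge, use baseline-adjusted observed T3 scores.
- Report mean (SD) change from observed pairs, with the number missing per arm and timepoint.
- Do not carry a waitlist T3 score to T4.
- Keep LOCF at most as a sensitivity analysis.
- State the missing-at-random assumption, and say that observed-pair and observed-T3 results leave out women without those scores.
- Record the switch as a dated change, because data collection ended in December 2024 and the article describes analysis as ongoing.

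The cost is a little extra analysis work, a few sentences of text and a convergence check with nine women. The model would also take the place of the planned repeated-measures ANOVA for these outcomes, and the dated change should say so.
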